ICBT may be applied as an alternative or in addition to psychotherapeutic and psychiatric care. These therapies are low-threshold psychosocial interventions and are effective in reducing symptoms, especially for depression, anxiety disorders, panic disorders, and social phobia, and are highly accepted by patients [17-19]. In NPPV, we integrated the digital mental health program called Novego, which has been found to be effective in the reduction of anxiety and depressive symptoms in general and in patients with schizophrenia [20-22]. Novego offers 3 different courses with a focus on depression, burnout, or anxiety. The managing physician or psychotherapist can generate an access code to these courses for a patient. With these codes, patients are able to follow the courses on the internet in their own pace. The administrative tasks related to the courses are carried out by the NPPV coordination office.

Beside the central coordination office, health care providers in the NPPV network are supported by regional network managers. Tasks of the network managers are recruitment of new network members, implementation of trainings for the professionals, organization of regular quality circles, administrative support for professionals, and quality management. Additionally, physicians and psychotherapists are connected with a common web-based infrastructure (“IVPnet”) for patient administration, treatment management, and communication.

The program is funded by the Innovation Fund (“Innovationsfonds”), which was established to support innovative health care projects in Germany in 2015, and financed by the statutory health insurance (SHI) system.

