### Study Population and Recruitment

We plan to recruit up to 14,000 patients for the intervention group in the region of North Rhine, Germany. The enrollment period begins in December 2017 and ends in June 2021. Patients eligible for participation in the NPPV program will be identified by their regular outpatient or inpatient health care providers or by their nursing home. They will be referred to a physician or therapist within the NPPV network, who does an entry examination to check eligibility. Inclusion criteria are as follows: age≥18 years, insurance in one of the participating health insurance companies (“AOK Rheinland/Hamburg,” “Continentale BKK,” and “BKK Deutsche Bank”), and 1 or more medical condition of 7 indication groups as outlined in Table 1. Participation in the NPPV program is voluntary. All patients need to give written informed consent to participate in the program and accompanied study.

**Table 1 table1:** Medical inclusion and exclusion criteria for indication groups.

Indication group	ICD-10-GM-Codes^a^	Additional criteria
Affective disorders (including anxiety and depression, excluding mania and bipolar disorder)	F30-F39, F41.2	Inclusion when more than 3 weeks unable to work OR at least 2 hospitalizations in 2 years OR minimum score in Mini-ICF Rating for mental disorders
Psychosis (including mania and bipolar disorder)	F20- F31	Inclusion of all patients
Posttraumatic stress or adjustment disorder	F43	Inclusion of all patients
Dementia	F00, F01, G30	Inclusion of all patients
Multiple sclerosis	G35	Inclusion of all patients
Parkinson disease	G20-G22	Inclusion of all patients except vascular parkinsonism (G21.4)
Stroke	I63-I64	Inclusion of all patients with dysfunctions or disabilities, for example, spasticity or cognitive impairment

^a^ICD-10-GM: International Statistical Classification of Diseases and Related Health Problems.

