#### SHI Routine Data

The participating health insurance companies (“AOK Rheinland/Hamburg,” “Continentale BKK,” and “BKK Deutsche Bank”) provide claims data on inpatient treatment, outpatient treatment, rehabilitation, drug prescriptions, and incapacity to work as well as basic personal information (eg, age, gender, and insurance periods) for participants as well as for 2 pools of control patients. Selection criteria for the first pool of control patients are ICD code of inclusion diagnosis (see Table 2; secured diagnosis of an outpatient health care provider that participates in the NPPV program), age≥18 years at time of diagnosis, and no participation in other special treatment contracts regarding the inclusion diagnoses (this is a pool to generate propensity scores for matching). The second pool consists of patients with the same selection criteria as the first pool, except that these patients should not be treated by a health care provider that is participating in the NPPV program (this is the pool to draw the control group via propensity score matching).

Data are provided at the end of the study and will include data from 4 quarters before inclusion date until March 2021 on each participant that started participation at least in March 2020 and control patients. Inclusion dates for potential control patients are determined by date of inclusion diagnosis. The permission to use the routine data of the participating insurance companies was granted by the State Ministry of Employment, Health and Social Affairs in North Rhine Westphalia.

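### The rule keeping patients of NPPV providers out of the control pool carries no date, so read literally it allows controls to be selected on provider contact after their index date

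*Protocol article*

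**What the plan says.** All places are in the protocol article.

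- **SHI Routine Data, pool 1** (used to estimate the propensity score). The qualifying diagnosis is a "secured diagnosis of an outpatient health care provider that participates in the NPPV program".
- **SHI Routine Data, pool 2** (source of the matched controls). The pool 1 criteria carry over with a single exception, which reads: "these patients should not be treated by a health care provider that is participating in the NPPV program".
- **Time zero for controls.** "Inclusion dates for potential control patients are determined by date of inclusion diagnosis".
- **Data window.** "Data are provided at the end of the study and will include data from 4 quarters before inclusion date until March 2021".
- **Network** (Intervention: The NPPV Program). "Tasks of the network managers are recruitment of new network members".
- **Route into the programme** (Study Population and Recruitment). "Patients eligible for participation in the NPPV program will be identified by their regular outpatient or inpatient health care providers or by their nursing home"; these patients are then referred into the network.
- **Use of pool 2** (Analyses in SHI Routine Data). It supplies the controls for the primary outcome, SHI expenditure over 12 months, and for secondary outcomes 1 to 5. Matching uses characteristics from the 12 months before inclusion.

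The article does not say when treatment or provider participation is to be judged, or how a control who later reaches an NPPV provider or enrols is handled.

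**The concern.** A control group for a 12-month cost comparison should be definable from what is known at time zero. The pool 2 condition does not ensure this. It is set at patient level, has no time limit, and is applied to data that extend well beyond the index date.

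Take a regular-care patient with an index diagnosis in 2018 who worsens some months later and is seen by a network specialist. Under the literal rule this patient leaves the control pool because of an event during follow-up. Nothing comparable is required of participants. Provider status raises the same problem: a control diagnosed in 2018 by a physician who joins in 2020 can be classed either way.

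At stake is the primary contrast. Strengths and Limitations says that acutely greater severity makes programme entry more likely and is not reflected in the routine data used for matching. If the patients who later reach NPPV are the costlier ones, removing them makes regular care look cheaper than it is. Matching on pre-index characteristics cannot put them back.

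**Working it through.** **1. The plan's own figure.** Sample Size Calculation assumes a 10% reduction, a coefficient of variation of 0.96, α = .05 and 80% power. With the control mean set to 1:

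n per group = 2 × (1.960 + 0.842)² × 0.96² / 0.10² = 1447 (two-sided).

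The plan states 1456, so the figure is reproduced within 0.6%. Power at 1456 per group is 80.3%. The sample size is not in question; it provides the yardstick of 10%.

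**2. How far past index the data reach.** Assume control index dates span the same period as the participants in the routine data, December 2017 to March 2020. The data then run about 39 months past the earliest index date (December 2017 to March 2021) and 12 months past the latest. For early controls, an undated rule could act on contact within the 12-month outcome window and also after it.

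**3. The two readings side by side.**

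- *Tied to the index diagnosis.* Pool 2 repeats the pool 1 criteria with one exception, and the pool 1 criterion concerns the provider who made the diagnosis. That diagnosis also sets the control's index date. The survey control rule (Patient Survey Data) is expressly tied to the provider of the inclusion diagnosis.
- *Literal.* Pool 2 does not repeat the diagnosis wording. It changes to treatment, without a date. The survey rule shows that the authors named the diagnosis when they meant it.

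Both readings are open. Only the literal one selects on follow-up.

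**4. Possible size under the literal reading.** Let q be the share of otherwise eligible controls removed for later contact, and r their mean cost relative to those retained. Both are **assumed**, and r must be a ratio that remains after matching and regression adjustment. With the mean of all eligible controls set to 1:

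- mean of retained controls: m = 1 / (1 − q + q·r)
- apparent reduction when the true one is 10%: 1 − 0.9 / m

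Example, q = 0.10 and r = 1.5: m = 1 / (0.90 + 0.15) = 1 / 1.05 = 0.952, a fall of 4.8%. Apparent reduction = 1 − 0.9 × 1.05 = 5.5%.

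| q | r | Change in control mean | Apparent reduction | Power at 1456 per group (SD 0.96) |
|---|---|---|---|---|
| 5% | 0.8 | +1.0% | 10.9% | 0.87 |
| 5% | 1.5 | −2.4% | 7.8% | 0.57 |
| 5% | 2.0 | −4.8% | 5.5% | 0.31 |
| 10% | 0.8 | +2.0% | 11.8% | 0.92 |
| 10% | 1.0 | 0 | 10.0% | 0.80 |
| 10% | 1.25 | −2.4% | 7.8% | 0.57 |
| 10% | 1.5 | −4.8% | 5.5% | 0.31 |
| 10% | 2.0 | −9.1% | 1.0% | 0.04 |
| 20% | 0.8 | +4.2% | 13.6% | 0.98 |
| 20% | 1.5 | −9.1% | 1.0% | 0.04 |
| 20% | 2.0 | −16.7% | −8.0% (an increase) | 0.00 |

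The power column refers only to the planned minimum. More patients would make the estimate more precise but would not remove the bias.

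**The case against.** The strongest reply is that the rule concerns the provider of the index diagnosis. The repeat of the pool 1 criteria with one exception and the parallel survey rule support this. If so, nobody is selected on follow-up. This reading stands as a possibility, but the text does not state it, and even then the date at which a provider counts as participating stays open.

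A second reply is that delivery of data at study end does not say when eligibility is judged, since claims can be queried as of any date. That is correct. The late delivery makes selection on later events possible; it does not show that it happened.

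A third is that a condensed article leaves query details to the full protocol. That would answer a missing detail. Here the selection rule is stated, and its wording permits conditioning on post-index events.

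A reader might also infer three stronger things that the documents do not support:

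- *That controls were in fact chosen on follow-up and crossovers dropped.* This follows only from the literal reading.
- *That the bias must run against NPPV.* No crossover share or cost ratio is given. The severity remark concerns programme entry, not any later contact with a network provider. With a ratio below 1 the sign reverses.
- *That checking at index would be a second defect because crossovers then stay among the controls.* Keeping them under their index status is sound; it only needs to be stated and their share reported.

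Finally, a ratio such as 1.5 in the raw pool could shrink after matching and adjustment. The table therefore applies only to a residual ratio.

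**Conclusion.** The point holds in conditional form. The exclusion that defines the control pool is undated, for treatment and for provider participation alike. Read literally, it lets controls be selected on events after time zero while participants are not. A benign reading is available but has to be inferred.

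A bias against NPPV is the more plausible direction, given what the article says about severity, but the documents settle neither sign nor size. Under assumed values of 5% to 20% removed and residual cost ratios of 0.8 to 2.0, a true 10% saving could appear as anything from a 13.6% saving to an 8.0% increase. With a ratio of 1, or if the rule was applied at index, this bias is absent. A possible distortion of the order of the effect sought justifies fixing the rule. It does not show that the result is wrong.

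**What to change.** Define the pool 2 condition only from information up to the control's index date: the provider of the index diagnosis and any treatment in the look-back period, with provider participation taken as of that date.

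Keep controls who later see an NPPV provider or enrol in the primary analysis under their index status, and report their share.

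As a sensitivity analysis, either compare the result with that from the never-treated pool, to show how much the rule matters, or censor controls at crossover with inverse-probability-of-censoring weights. Censoring without weights should be avoided: it depends again on a post-index event and cuts short a cumulative 12-month cost.

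Cost: a re-run of the selection query with provider joining dates and NPPV enrolment dates, possibly with a further data draw, renewed matching, and one sensitivity analysis. The statistical price is slight dilution from controls who cross over later. The article reports that data analysis was completed in 2022. If it cannot be reopened, the report should at least state which rule was applied and give the sensitivity result.

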### Study Outcomes and Data Sources

#### Overview

The primary study outcome is the overall SHI expenditures per patient in 12 months after inclusion. Secondary outcomes include SHI expenditures for psychiatric and neurological treatments, hospitalizations (frequency and length of stay), patient-related outcomes (ie, health-related quality of life, satisfaction with health care, and use of intervention modules), and provider-related outcomes (ie, satisfaction, structure and process quality, and needs-led approach).

Data to evaluate the outcomes stem from SHI routine data, outpatient claims data, drug prescription data, a patient survey, and a provider survey. All outcomes and the corresponding data sources are summarized in Table 2.

**Table 2 table2:** Study outcomes and data sources.

Outcomes			Data source

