#### Analyses in SHI Routine Data

SHI routine data are used to evaluate the primary outcome and the secondary outcomes 1-5 (see Table 2). For all outcomes, NPPV participants are compared to a control group that is matched by propensity score matching [30]. Propensity scores are calculated using the data of the first pool of control patients and the participants in a multiple regression model estimating probability of participation in the NPPV program by personal (eg, age and gender) and health characteristics in the 12 months before inclusion date (eg, hospitalizations and frequency of out-patient treatments). The control group consists of matched persons of the second pool of control patients using the estimated propensity scores. To evaluate the outcomes, multiple regression models are estimated, controlling for relevant confounders. If necessary (high intraclass correlation coefficient), multilevel models are used to account for the hierarchical data structure (patients nested in outpatient health care providers that participate in NPPV).

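### Participants and controls in the routine-data comparison start their clocks at different events, with no stated alignment, so the primary cost comparison may be biased in either direction

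*Protocol article*

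**What the plan says.** All places are in the protocol article.

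- **Outcome window** (Study Outcomes and Data Sources, Overview): "The primary study outcome is the overall SHI expenditures per patient in 12 months after inclusion".
- **Participant entry** (Study Population and Recruitment): regular providers or nursing homes identify patients. "They will be referred to a physician or therapist within the NPPV network, who does an entry examination to check eligibility". The data request in SHI Routine Data then dates participants by programme start: "on each participant that started participation at least in March 2020 and control patients".
- **Control entry** (SHI Routine Data): "Inclusion dates for potential control patients are determined by date of inclusion diagnosis". The first control pool needs a "secured diagnosis of an outpatient health care provider that participates in the NPPV program". The second pool, from which controls are drawn, has the same criteria except that the provider is outside the programme.
- **Baseline for the propensity score** (Analyses in SHI Routine Data): personal characteristics and "health characteristics in the 12 months before inclusion date (eg, hospitalizations and frequency of out-patient treatments").
- **Calendar frame**: "The enrollment period begins in December 2017 and ends in June 2021" (Study Population and Recruitment). The routine data "will include data from 4 quarters before inclusion date until March 2021" (SHI Routine Data). No calendar window is given for the control diagnosis dates.

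**The concern.** In a matched cohort, the start of follow-up should mean the same thing in both groups. Here one group starts at entry to a care programme and the other at a coded diagnosis. A participant can enter at any point in a long illness. Table 1 admits all patients with multiple sclerosis or dementia, and nearly all with Parkinson disease. For affective disorders, two of the three routes (more than 3 weeks unable to work, or at least 2 hospitalizations in 2 years) describe illness already under way. The listed control criteria are ICD code, age and no other special contract.

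If the control date tends to fall at a different stage of illness, the outcome year differs in kind between the groups, and so does the baseline year that feeds the propensity score. Good balance on prior-year hospitalizations would then be weak evidence of comparability, because the prior year precedes a diagnosis in one group and an enrolment in the other. The primary outcome and secondary outcomes 1-5 all use this control group.

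**Working it through.** **Step 1. The two clocks side by side**

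| | Participants | Potential controls |
|---|---|---|
| Event at time zero | Programme start | Date of inclusion diagnosis |
| Baseline | 12 months before that event | 12 months before that event |
| Outcome | 12 months after that event | 12 months after that event |
| Stated link to the other group's date | none | none |

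The mismatch in the defining event is stated in the text. What follows from it depends on how the control date is read:

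- *First coding of the diagnosis.* Controls would contribute the year after a new diagnosis and a baseline from before it, while many participants would contribute years of established disease.
- *Any secured coding.* Patients with long-standing disease qualify as controls and the difference in phase shrinks, but the date still has no stated link to the enrolment date of the matched participant.

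**Step 2. Calendar time**

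I read the March 2020 limit as the latest programme start, since 12 months of follow-up then end in March 2021. A December 2017 start has its outcome year ending about December 2018, and a March 2020 start has it ending in March 2021. The article itself refers to the COVID-19 pandemic (Provider Survey; Discussion). Calendar quarter could therefore matter for cost, and no matching on it is described.

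**Step 3. The plan's own sample size**

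Inputs from Sample Size Calculation: 10% reduction, coefficient of variation 0.96, power 80%, α = 0.05, equal groups. I take the test as two-sided; one-sided gives 1140, which does not fit.

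n per group = 2 × (1.960 + 0.842)² × 0.96² / 0.10² = 1447

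The article states 1456, so its figure reproduces closely. Power at 1456 per group is 80.3%.

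**Step 4. What a shift would do (illustration; every shift is assumed)**

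The documents give no size for the bias. Let k be the relative shift in mean control cost caused by the clock alone.

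Apparent saving with no true effect = 1 − 1/(1 + k)

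- k = +5%: 1 − 1/1.05 = 4.8% apparent saving
- k = −5%: 1 − 1/0.95 = −5.3%, an apparent extra cost

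With a true saving of 10%, the apparent saving is 1 − 0.90/(1 + k): 14.3% at k = +5% and 5.3% at k = −5%.

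The chance of a significant result with no true effect, for a shift of b (as a fraction of mean cost), uses z = b / (0.96 × √(2/n)). At n = 1456 and b = 0.05, z = 0.05/0.0356 = 1.41, and the two-sided 5% test rejects in 29.0% of cases.

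| Assumed shift b | Rejects at 1456 per group | Rejects at 14,000 per group |
|---|---|---|
| 0 | 5.0% | 5.0% |
| 2% | 8.7% | 41.4% |
| 3% | 13.5% | 74.4% |
| 5% | 29.0% | 99.2% |
| 10% | 80.3% | about 100% |

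The 14,000 column is an upper bound. It is the recruitment ceiling, and only starts up to about March 2020 enter this analysis.

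In the other direction, if the true saving is 10% and the shift hides 2, 3 or 5 points of it, power at 1456 per group falls to 61%, 50% or 29%.

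A larger sample does not remove the shift; it makes a false result more certain.

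**The case against.** The strongest reply is that the article fixes less than the concern supposes.

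1. *The diagnosis is not said to be a first one.* This stands. A reader might infer that controls contribute an expensive work-up year, but the text requires only a secured diagnosis, which a long-standing patient also has.
2. *No calendar mismatch is stated.* This also stands. With no window for control dates, different calendar periods are neither shown nor excluded.
3. *The covariates are only examples, and the outcome models control for relevant confounders.* This stands in part. Index quarter or time since diagnosis may be among them in a fuller document, and prior-year utilisation will partly separate patients already in care from new ones. It would be wrong to say that matching cannot reduce the bias. But the covariates are measured on the same unaligned clocks, so matching cannot be relied on to remove it.
4. *The bias may run against the programme.* This stands. Strengths and Limitations says that acutely higher severity makes inclusion more likely and is not captured in the matching data. Participants may enter at a costly moment, which would hide a saving. A reader might infer a spurious saving; the document does not support choosing that direction. The same section does not mention the difference in time zero.
5. *The fix still uses a coded diagnosis.* True, and compatible with the article's rule. What it adds is the missing link: which coding counts, and in which quarter.

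The reply narrows the point but does not remove it. The article states the index rule itself, so the concern is not merely about a detail left to another document.

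**Conclusion.** The point holds as a risk built into the definition of the primary contrast. Time zero is set by different events in the two groups, and the article describes no step that aligns them on calendar quarter or on new versus established diagnosis. Under either reading of the control date, its link to the matched participant's enrolment is unstated.

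Not established are that disease phases or calendar periods do differ, how large any bias is, and which way it runs. The figures above rest on assumed shifts and on the plan's coefficient of variation. They show only that a shift of 5% in either direction would be about half the planned effect. Confidence is high for the mismatch and low for its consequence. It should be resolved before a saving, or the absence of one, is attributed to the programme.

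**What to change.** **Change**

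- State what the date of the inclusion diagnosis means: the first coding, or any secured coding in a defined window.
- For a participant enrolled in quarter q, draw controls with a qualifying diagnosis coded in q by an outpatient provider outside the programme, and make q the control's index quarter. Index the first pool, used to estimate the score, in the same way with its own provider criterion.
- Match exactly on calendar quarter and on new versus already-coded diagnosis in the preceding 4 quarters, with the propensity score used within these strata.
- Measure covariates in the 4 quarters before the index and costs in the 12 months after it, in both groups.
- Re-index only to quarters for which the delivered data give a full 4-quarter baseline and 12 months of follow-up. Delivery starts 4 quarters before the control's existing inclusion date, so an earlier index would lack baseline.

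**Cost**

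No new data collection is evident, provided that the delivered outpatient claims carry the diagnosis codes. The Results section reports the analysis as complete, so the matching and the models for the primary outcome and secondary outcomes 1-5 would have to be rerun. Some controls will be lost to exact matching. The change does not alter the required sample size, and it does not remove the acute-severity difference that the article already concedes.

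If the completed primary analysis is kept, report the aligned-index analysis beside it before any saving is claimed.
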